#### 6.4.1 Outcome Assessors

Two qualified neurodevelopmental specialist doctors (child psychiatrists and/or pediatric neurologists) from each of the eight participating sites with more than five years of experience will be responsible for baseline and post-

treatment evaluation. All medical personnel participating in the outcome assessment process will be required to undergo mandatory 2-day refresher training on standardized assessments of ATEC, ABC, and CSHQ to reduce rater bias. Training will take place before study commencement in person in each of the site. The outcome assessors are forbidden to be involved in the subject randomized allocation to the two groups and will be blinded. The outcome assessors will also not participate in the treatment of the subjects.

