### 1.5 Rationale for Study Design

The study will be designed as a multi-center, sham-controlled, double-blinded, randomized controlled trial to investigate effects of tPCS in improving social functioning and sleep in children with ASD aged 3-14 years old. Both the intervention and control group will both receive standard of care behavioural therapy for ASD in China (i.e ABA therapy, structured teaching, play therapy and speech therapy). In addition, the intervention group will receive active tPCS stimulation while the control group will receive sham tPCS stimulation, during the period of the trial (20 sessions over one month), this will ensure that any estimated treatment differences between groups is unlikely due to placebo effects. All doctors performing pre-post treatment evaluation will be blinded to the allocation of participants to the two groups, participants and their accompany caretakers will also be blinded, thus it will be a double-blind design. The trial recruitment and execution will take place in eight different sites in the Guangdong province in China, to avoid site-specific bias and to verify the feasibility of tPCS in varying clinical environments with patients from different socio-economic backgrounds. The double blinding, sham-controlled, multi-site design will ensure minimal bias to be introduced that may exert confounding effects to the study results.

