### Autism Treatment Evaluation Checklist (ATEC)

ATEC is developed by the Autism Research Institute and designed as a one-page checklist. Comprising 77 items, the ATEC has been utilized to assess the efficacy of interventions by measuring changes in response to various treatment modalities for children with ASD. The ATEC consists of four subscales totaling 77 items:

- Scale I: Speech, Language, and Communication (14 items, with scores ranging from 0 to 28)
- Scale II: Sociability (20 items, with scores ranging from 0 to 40)
- Scale III: Sensory and Cognitive Awareness (18 items, with scores ranging from 0 to 36)
- Scale IV: Health, Physical Condition, and Behavior (25 items, with scores ranging from 0 to 75)

Each category within the ATEC utilizes a four-point rating scale to gauge the severity of issues, ranging from 0 (indicating no problem) to 3 (indicating a serious problem). The ATEC generates a total score ranging from 0 to 179, with higher scores indicating a greater degree of reported activity limitations. This comprehensive assessment tool enables researchers and clinicians to gain insight into the challenges faced by individuals with ASD and to monitor changes in symptoms and functioning over time. For this study, the ATEC will be administered twice (pre- and post-tPCS) and carried out by an experienced therapist or doctor who is blinded regarding the subject allocation.

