### **3 Autism Behaviour Checklist (ABC)**

The Autism Behavior Checklist is a classic screening tool for autism. Comprising 57 items and organized into five subscales—sensory behavior, social relating, body and object use, language and communication skills, and social and adaptive skills—the checklist assigns scores ranging from 1 to 4 per item, with higher scores indicating more severe symptoms. A total score of <53 is considered a negative screening test, a total score of ≥53 and ≤67 is considered a positive screening test, and a total score of ≥68 can assist in the diagnosis of autism. In this study, the ABC will be administered twice (pre- and post-tPCS) by an experienced therapist or doctor in clinic, who is blinded regarding the subject allocation.

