### **4 Children's Sleep Habits Questionnaire (CSHQ)**

The Children's Sleep Habits Questionnaire (CSHQ) is a retrospective assessment tool to investigate sleep patterns in young children consisting of 45 items designed for parents to report on their child's sleep behavior. The CSHQ covers various sleep domains, including bedtime behavior and sleep onset; sleep duration; anxiety around sleep; behavior occurring during sleep and night wakings; sleep-disordered breathing; parasomnias; and morning waking/daytime sleepiness. Each item is rated on a three-point scale: "usually" if the behavior occurred five to seven times per week, "sometimes" for two to four times per week, and "rarely" for zero to one time per week. In this study, the CSHQ will be administered twice (pre- and post-tPCS) by experienced therapists who is blinded regarding the subject allocation through interviewing parents or caregivers in clinic.

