#### 6.2.4 One day (approximately 3 hours) of post-treatment assessment of ATEC, ABC and CSHQ, performed by qualified occupational therapists and child psychologists, through clinical observation and parent interviews.

### 6.3 Specific treatment adherence requirements/strategies

In this study, the tPCS intervention will be provided to participants free-of-charge in the eight hospital sites. The participants will not receive any monetary payments or gifts for their participation in the study.

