## Appendix 2 – Data Form (ABC)

### Autism Behaviour Checklist

Child's Name: \_\_\_\_\_ Gender: \_\_\_\_ Date of Birth: \_\_\_\_\_ Year \_\_\_\_ Month \_\_\_\_ Day

Relationship to the Child: \_\_\_\_\_ Contact Information: \_\_\_\_\_

Date of Form Completion: \_\_\_\_\_ Year \_\_\_\_ Month \_\_\_\_ Day

(Note: The person filling out the form should be the child's parents or someone who has lived with the child for more than two weeks.)

This form lists 57 items related to the child's sensory, behavioral, emotional, and language abnormalities. This form lists 57 items related to the child's sensory, behavioral, emotional, and language abnormalities. Circle the number for those items most accurately describing the child. Do not miss any items.

Note: Sensory Ability (S), Relating Ability (R), Body & Object Use (B), Language Ability (L), and Social & Self-Help Ability (S)

| Item                                                                                                         | Score |   |   |   |   |
|--------------------------------------------------------------------------------------------------------------|-------|---|---|---|---|
|                                                                                                              | S     | R | B | L | S |
| Whirls self for long periods of time                                                                         |       |   | 4 |   |   |
| Learns a simple task but "forgets" quickly                                                                   |       |   |   |   | 2 |
| Frequently does not attend to social/environmental cues                                                      |       | 4 |   |   |   |
| Does not follow simple commands (sit down, come here, stand up) given once                                   |       |   |   | 1 |   |
| Does not use toys appropriately (spins wheels, etc.)                                                         |       |   | 2 |   |   |
| Poor use of visual discrimination when learning (fixates on parts of objects such as size, colour, position) | 2     |   |   |   |   |
| Lacks a social smile (may smile out of context)                                                              |       | 2 |   |   |   |
| Exhibits pronoun reversal (For example, saying 'I' instead of 'you,' etc.)                                   |       |   |   | 3 |   |

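### The protocol conflicts on who rates the outcomes and does not fix assessor or informant across the two visits, so part of a change score can be a change of person

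*Combined protocol and SAP*

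**What the plan says.** Who rates:

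- **6.4.1 (Outcome Assessors):** "Two qualified neurodevelopmental specialist doctors (child psychiatrists and/or pediatric neurologists) from each of the eight participating sites" are responsible for baseline and post-treatment evaluation. Section 1.5 also describes the evaluators as doctors: "All doctors performing pre-post treatment evaluation will be blinded to the allocation of participants to the two groups".
- **6.2.1 (baseline) and 6.2.4 (post-treatment):** both assessments are "performed by qualified occupational therapists and child psychologists, through clinical observation and parent interviews".
- **Notes to the visit table in 4.3:** the ATEC is "carried out by an experienced therapist or doctor who is blinded regarding the subject allocation", and the ABC is administered "by an experienced therapist or doctor in clinic, who is blinded regarding the subject allocation". The CSHQ is administered "by experienced therapists who is blinded regarding the subject allocation through interviewing parents or caregivers in clinic".

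Who supplies the information:

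- The CSHQ note accepts parents or caregivers without naming one person.
- The ABC form in Appendix 2 accepts a parent or "someone who has lived with the child for more than two weeks".

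Sections 2.2 and 2.3 define all outcomes (ATEC, ABC, CSHQ) as change from baseline to post-treatment, and 4.3 schedules one rating at each of those two points.

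Safeguards already present: assessors are blinded and take no part in allocation or treatment (6.4, 6.4.1), and they receive two days of training on the three scales before the study starts (6.4.1). The ATEC and CSHQ forms record who completed them and that person's relationship to the child. The ABC form records the relationship.

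**The concern.** The professions in 6.4.1 and in 6.2.1/6.2.4 do not overlap, so a site cannot follow both literally. Even under 6.4.1 alone there are two assessors per site and no rule that pairs a child with one of them. The informant is equally free to differ between visits.

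With only two ratings per child, any difference between raters or informants goes straight into the change score when the person changes. It lowers the correlation between baseline and week 4, which widens the change score and weakens baseline adjustment. Training before the study limits this, but the plan sets no agreement threshold and the analysis in 9.2 takes no account of rater or informant. The forms shown have no assessor ID, so a change of assessor may not be recoverable from the data afterwards.

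**Working it through.** **1. The plan's own figure.** Section 9.1 gives effect size 0.36, 80% power, 5% alpha and 120 per group. Its wording mixes paired, two-sided and one-sided terms. The reading that comes close to 120 is a two-sample, two-sided test:

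n = 2 × [(1.96 + 0.84)/0.36]² ≈ 121.1 per group (122.1 with the t distribution).

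This is within 2% of 120. With exactly 120 per group, t-test power is 79.3%.

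**2. Model for a switch.** Let *f* be the share of children whose rater or informant changes. Let *v* be the variance that a change adds, as a multiple of the change-score variance with the same person twice. The documents give neither, so both are assumptions. Then:

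- variance ratio = 1 + f·v
- effective d = 0.36/√(1 + f·v)

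**3. Results at f = 0.2, 120 per group, two-sided 0.05:**

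| v | Variance ratio | Effective d | Power |
|---|---|---|---|
| 0 | 1.00 | 0.360 | 79.3% |
| 0.10 | 1.02 | 0.356 | 78.5% |
| 0.25 | 1.05 | 0.351 | 77.3% |
| 0.50 | 1.10 | 0.343 | 75.4% |
| 1.0 | 1.20 | 0.329 | 72% |
| 1.5 | 1.30 | 0.316 | 68% |

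The last two rows correspond to a marked fall in correlation. With equal variances at both visits, set to 1, the change variance is 2(1 − r). At r = 0.8 this is 0.4. If a switch lowers r to 0.6 it is 0.8, so v = (0.8 − 0.4)/0.4 = 1.0. If r falls to 0.5 it is 1.0, so v = (1.0 − 0.4)/0.4 = 1.5. If 40% switch at these severe values, the ratios are 1.40 and 1.60 and power is 65% and 59%.

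**4. Baseline-adjusted analysis.** Section 9.2.1 includes ANCOVA. Hold the raw effect fixed at 0.36 × √0.4 = 0.228 and use residual variance 1 − r̄², where r̄ is the average correlation.

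- No switching: r̄ = 0.80, residual variance 0.36, d = 0.379, power 83%.
- 20% switching, r = 0.5 or 0.6 after a switch: r̄ = 0.74 or 0.76, residual variance 0.452 or 0.422, power 74% or 77%.
- 40% switching: r̄ = 0.68 or 0.72, residual variance 0.538 or 0.482, power 67% or 72%.

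**5. Type I error.** In 20,000 simulated trials with 120 per arm, no treatment effect and half of the children switching regardless of arm, the rejection rate was 4.9% at v = 0.5 and 5.2% at v = 1.0. Both are consistent with the nominal 5%.

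**6. Reserve.** If the planned 40% dropout occurs, 170 × 0.6 = 102 per arm remain. Power is then about 73% before any switching.

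**The case against.** The best defence is that each account is consistent over time. Section 6.4.1 makes the same two doctors per site responsible for both time points, and 6.2.1 and 6.2.4 name the same professions and the same method at both. Section 6.4.1 can also be read as putting doctors in charge while other trained staff carry out the ratings. The therapist-or-doctor wording in the notes to 4.3 is broad and need not be a separate account. The ABC form's note concerns the informant and not the assessor. Training, blinding and the recorded relationship already limit or expose part of the problem.

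Much of this stands. It means that a reader who inferred that every change score contains a change of person would go too far: no section prescribes a switch, and a child rated twice by the same assessor from the same caregiver has no such component. It does not remove the point, because consistency of profession is not identity of person.

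A reader might also infer bias between arms. That would require switching to differ by arm. The documents give no sign of this: caregivers and assessors are blinded and the visit schedule is the same in both arms.

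Finally, the 0.36 is an average of effect sizes from other studies and may already contain some rater noise, in which case the calculation counts part of the loss twice.

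**Conclusion.** The conflict over who rates is real and has to be reconciled. The absence of any same-assessor or same-informant rule is also real, and it matters because every efficacy endpoint is a two-point change score. The consequence the documents support is lost precision. Under the assumptions shown, with 20% of children switching, power falls from 79% by roughly 1 to 4 points if a switch adds 0.1–0.5 times the same-person change variance, and by 7 to 11 points if it adds 1.0–1.5 times. Only the direction is firm, because switch rate and added variance are assumed throughout. Inflated type I error and bias between arms are not supported. The point is worth acting on because the remedy is cheap and cannot be applied after the ratings are made.

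**What to change.** 1. Reconcile 1.5, the ATEC, ABC and CSHQ notes in 4.3, 6.2.1, 6.2.4 and 6.4.1 to one assessor group per scale.
2. Require that each child's ATEC, ABC and CSHQ be rated at Visit 22 by the assessor who rated Visit 1, from the same main caregiver, who is named as informant at consent.
3. Add an assessor ID to the three forms. They already record the informant's relationship to the child.
4. If the same assessor or caregiver cannot attend, rate the child anyway, flag the switch and keep the child in the main analysis. Report a supportive sensitivity analysis, for example with a switch indicator. Leaving out switched pairs is a post-randomisation exclusion, so it can be supportive only.

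The cost is protocol wording, one extra form field and less freedom in scheduling Visit 22. Under the 6.4.1 account two assessors per site already exist. Whether other staffing is needed depends on which account the sponsor adopts.

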#### 6.4.2 Subjects

Subjects in the intervention group will be given active-tPCS stimulation and subjects in the Control group will be given sham-tPCS stimulation. The subjects and their parents / caretakers will be blinded according to Section 6.4.

## 7 Safety Measurements

### 7.1 Definitions

An adverse event (AE) is any untoward medical occurrence in a clinical investigation subject who is administered a medicinal product or investigational product, and which does not necessarily have a causal relationship with this treatment. An adverse event (AE) can therefore be any unfavorable and unintended sign (including an abnormal laboratory finding), symptom, or disease temporally associated with the use of a medicinal (investigational) product, whether or not related to the medicinal (investigational) product. A serious adverse event (SAE) is any untoward medical occurrence that at any dose:

- results in death
- is life-threatening
- requires inpatient hospitalization or prolongation of existing hospitalization
- results in persistent or significant disability/incapacity, or
- is a congenital anomaly/birth defect

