### 1.2.3 Safety of tES in Children

While there are yet no studies done involving tPCS and children with ASD, the safety of tPCS had been

investigated in childhood cerebral palsy and in adult neurological disorders such as Parkinson's disease, chronic visceral pain and disorder of consciousness, with no adverse events recorded. At present, it is generally considered that an output current between 0-2mA, and the single stimulation time is less than 40 minutes is considered relatively safe. There is no exact guidelines for tES dosing in children although a dose of up to 1mA is typically used. Krishnan C et.al conducted a comprehensive statistical analysis of 48 clinical studies involving more than 513 children and / or adolescents with non-invasive brain stimulation. They found that the most common adverse reaction of tES among people under 18 years of age was skin tingling, with an incidence rate of 11.5%, followed by skin itching, with an incidence rate of 5.8%. These adverse reactions were transient and non-persistent. In terms of cognitive adverse events, treatment-emergent mania and hypomania have been reported in unipolar and bipolar depression treatment in tDCS trials in diseased adults. Finally, drug interactions with tDCS have been reported, with antipsychotics with high D2 affinity such as Haloperidol and Risperidone reported to suppress neuromodulation-induced plasticity while benzodiazepines were associated with an increase in depression scores when used in conjunction with tDCS.

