### 3.6 Exclusion Criteria

- A. Those who do not meet the above inclusion criteria;
- B. Subjects <3 years or >14 years old;
- C. Subjects with IQ score  $\leq 35$  , according to WISC (4th edition)
- D. Subjects with comorbid epilepsy or history of epileptic disorders
- E. Subjects with presence of severe psychiatric disorders such as schizophrenia and psychosis, or a family history of schizophrenia and psychosis.
- F. Subjects diagnosed with obstructive sleep apnea.
- G. Subjects with skull defect or presence of severe scalp infection at the proposed site of stimulation.
- H. Subjects with a history of craniotomy, presence of any ferromagnetic metal or implanted medical devices in the head or body, e.g. cochlear implant, pacemaker or defibrillator, history of severe neurological disorders such as brain tumors and intracranial infection
- I. Subjects with history of substance abuse or dependence, use of benzodiazepines, neuroleptics and antipsychotic medications including risperidone and haloperidol.
- J. Subjects who have current involvement with other forms of non-invasive brain stimulation including transcranial magnetic stimulation or transcranial direct current stimulation.

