### 7.2 Collection, Recording and Reporting of Serious Adverse Events to Ethics Board

Only related SAEs (definitely/ probably/ possibly) will be reported to the Ethics Board of Nanhai Maternity and Children's Hospital of Guangzhou University of Chinese Medicine ( main hospital site) and the Foshan Science and Technology Bureau, Guangdong province. Related means there is a reasonable possibility that the event may have been caused by participation in the clinical trial. The investigator is responsible for informing the Ethics Board after first knowledge that the case qualifies for reporting. Follow-up information will be actively sought and submitted as it becomes available. Related AEs will not be reported to Ethics Board. However, the investigator is responsible to keep record of such AEs cases at the Study Site File.

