**IV. Health/Physical/Behavior:**

- |                                       |                                      |                                                                 |
|---------------------------------------|--------------------------------------|-----------------------------------------------------------------|
| N MI MO S 1. Bed-wetting              | N MI MO S 9. Hyperactive             | N MI MO S 18. Obsessive speech                                  |
| N MI MO S 2. Wets pants/diapers       | N MI MO S 10. Lethargic              | N MI MO S 19. Rigid routines                                    |
| N MI MO S 3. Soils pants/diapers      | N MI MO S 11. Hits or injures self   | N MI MO S 20. Shouts or screams                                 |
| N MI MO S 4. Diarrhea                 | N MI MO S 12. Hits or injures others | N MI MO S 21. Demands sameness                                  |
| N MI MO S 5. Constipation             | N MI MO S 13. Destructive            | N MI MO S 22. Often agitated                                    |
| N MI MO S 6. Sleep problems           | N MI MO S 14. Sound-sensitive        | N MI MO S 23. Not sensitive to pain                             |
| N MI MO S 7. Eats too much/too little | N MI MO S 15. Anxious/fearful        | N MI MO S 24. "Hooked" or fixated on
certain objects/topics  |
| N MI MO S 8. Extremely limited diet   | N MI MO S 16. Unhappy/crying         | N MI MO S 25. Repetitive movements
(stimming, rocking, etc.) |
|                                       | N MI MO S 17. Seizures               |                                                                 |

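### The SAE definition has no medically-important-event criterion, so a seizure or manic episode that is not admitted, life-threatening or disabling has no mandatory route to the Ethics Board or DSMC during the trial

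*Combined protocol and SAP*

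**What the plan says.** **Definition.** Section 7.1 lists five outcomes that make an event serious. The first is death. The others read: "is life-threatening"; "requires inpatient hospitalization or prolongation of existing hospitalization"; "results in persistent or significant disability/incapacity, or" finally "is a congenital anomaly/birth defect". The list ends there.

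**Ethics Board.** Section 7.2 sends on only those SAEs judged definitely, probably or possibly related. For non-serious events it is explicit: "Related AEs will not be reported to Ethics Board". The investigator keeps these in the site file.

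**DSMC.** Under A5.1 the principal investigator's monthly report contains data integrity reports and SAE summaries from each site. Emergency meetings are permitted over safety adverse events. Under A5.6 the committee meets every 6 months to discuss the monthly and interim reports.

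**Other handling of adverse events.** Caregivers complete an adverse event log after each session (Section 4.3, tPCS note). The investigators log and monitor events (Section 7.3). Section 9.2.3 plans an adverse event table for the full study population, with a chi-square test for comparing incidence between groups.

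**Where these kinds of event appear.** Section 1.2.3 records that "treatment-emergent mania and hypomania have been reported in unipolar and bipolar depression treatment in tDCS trials in diseased adults". Section 3.6 excludes "Subjects with comorbid epilepsy or history of epileptic disorders", and also excludes psychosis or a family history of it. Scale IV of the ATEC form in Appendix 1 contains "N MI MO S 17. Seizures".

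**The concern.** Seriousness criteria usually end with a judgement item, so that an event which matters medically but meets none of the listed outcomes can still be escalated. This list has no such item. In this protocol the SAE label also decides what leaves the investigators' hands: Section 7.2 uses it as the threshold for the Ethics Board, and A5.1 uses it for the committee's monthly safety content.

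Section 1.2.3 says that tPCS has not yet been studied in children with ASD, so the trial has no earlier safety experience in this population to rely on. A new seizure or manic episode is the kind of event on which an oversight body might want to reconsider risk and benefit while recruitment continues. As written, such an event could be known only to the investigators until the final safety table.

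Section 9.2.3 adds to the problem by describing possible side effects as confined to the skin under the electrodes. That conflicts with the mania reports in Section 1.2.3 and the headache listed in Section 2.4.1. It gives a site little reason to escalate a neuropsychiatric event on its own initiative.

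**Working it through.** No figure in the plan bears on this point, so the check is a trace of one event through the rules as written.

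**Test case A.** A child with no seizure history has a brief first seizure on the evening after a session and is seen as an outpatient. The event is neither life-threatening nor disabling. The investigator judges it definitely related.

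1. *Section 7.1, seriousness.* Death: no. Life-threatening: no. Admission or prolonged admission: no. Persistent or significant disability or incapacity: no. Congenital anomaly: no. It meets 0 of 5 criteria, so it is an adverse event and not an SAE.
2. *Section 7.2, Ethics Board.* Only related SAEs go forward. The event is related but not serious, and the rule on related AEs expressly keeps it back. It stays in the site file.
3. *A5.1, monthly DSMC report.* The listed content is data integrity reports and SAE summaries. The event is in neither.
4. *A5.2 to A5.4, interim report.* The interim analysis at 170 of 340 children covers ATEC, ABC, CSHQ and baseline characteristics. Adverse events are not listed.
5. *A5.1, emergency meeting.* One may be called, since the wording is not limited to SAEs. No trigger is stated and nothing requires it.
6. *Sections 4.3 and 7.3.* The event can be entered in the caregiver log at the next session, and the investigators monitor it.
7. *Section 9.2.3.* It is counted in the adverse event table.

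**Test case B.** The same event, but life-threatening or causing significant incapacity at home. It meets a Section 7.1 criterion without admission, so it is an SAE. It goes to the Ethics Board if judged related, and into the DSMC summary.

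| | Case A | Case B |
|---|---|---|
| Class under 7.1 | AE | SAE |
| Ethics Board, if related | Expressly not reported | Reported |
| Monthly DSMC report | Not in listed content | In SAE summary |
| DSMC emergency meeting | Discretionary | Discretionary |
| Investigators' log | Yes | Yes |
| Table in 9.2.3 | Yes | Yes |

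A manic, hypomanic or psychotic episode managed at home without significant incapacity follows the Case A column.

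**ATEC item 17.** Section 4.3 schedules the ATEC at Visit 1 and Visit 22, so a new seizure can be recorded as a change on the primary outcome form. No passage links a rating on that item to an adverse event entry. The caregiver log is tied to sessions, so for an event between the last session and Visit 22 the ATEC may be the only scheduled form that asks about seizures.

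**The case against.** The strongest reply is that the plan handles such events better than a quick reading suggests. Several parts of it stand.

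- *Admission is not the only gateway.* A reader might infer that a seizure or manic episode is serious only if the child is admitted. Section 7.1 does not say that. A life-threatening event qualifies, and so does one causing disability or incapacity that is either persistent or significant. The gap covers only events that meet none of these.
- *The DSMC is not barred from seeing adverse events.* A reader might infer that they can never reach it. A5.1 says what the monthly report will include, not that it is limited to that, and it allows emergency meetings over safety adverse events. The text just before A5.1 was not in the copy reviewed. What can be said is that the text reviewed states no routine or mandatory route.
- *The events are not lost.* A reader might infer that a report of no related SAEs would leave the trial without safety evidence. Section 9.2.3 tabulates adverse events, not only SAEs, so a seizure classed as an AE is still counted.
- *The documents do not name seizure as a tPCS risk.* It appears through the epilepsy exclusion and a checklist item. The mania reports concern adults with depression given tDCS. These passages show why the events deserve attention; they do not show that the events are expected.
- *No rate is given.* Any probability of seeing such an event among the 170 active children would rest on an invented rate.

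None of this answers steps 2 and 3 of the trace. The log, the investigators' monitoring and the final table are either internal to the study team or come at the end. None is a required report to an oversight body while children are still being treated.

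**Conclusion.** The concern holds in a limited form. Section 7.1 lacks a medically-important-event criterion. A related seizure or manic, hypomanic or psychotic episode that is not admitted, not life-threatening and not significantly disabling is therefore kept from the Ethics Board by an explicit rule. It is also absent from the listed content of the monthly DSMC report, which leaves a discretionary emergency meeting as the only stated route to the committee.

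The gap is in reporting to oversight bodies during the trial. Capture of events and the final adverse event table are not affected. The size cannot be expressed as a number, because the documents give no event rate and the finding does not depend on one. It rests on reading Sections 7.1, 7.2 and A5.1 as complete statements of their rules, with the stated limit on the Appendix 5 text. The change should be made, since it is cheap and the population has not been studied with this stimulation before. The point does not undermine the efficacy analysis.

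**What to change.** 1. **Section 7.1.** Add a sixth criterion: any other medically important event. Name at least any seizure and any manic, hypomanic or psychotic episode as meeting it, whether or not the child is admitted. These events then follow the existing SAE route: to the Ethics Board if judged related, and into the SAE summary in the monthly DSMC report. Sections 7.2 and A5.1 need no rewording for this.
2. **Section 4.3, ATEC note.** State that a rating above N on item 17 at the post-treatment visit is queried and, if confirmed as a seizure during the study, entered as an adverse event. A matching check at baseline would add little, because epilepsy is already screened for under Sections 3.5 and 3.6.

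The cost is a few sentences and a few more reports, using forms already completed. The change concerns classification and reporting only; clinical handling of such events stays with the investigators.
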